### Data collection

All those who participate in the Evaluation-Research package (Option 1), data will be collected by on-line survey links for HCPs, the supplied iSISTAQUIT practice software templates and routinely collected data from services’ databases (clinical information systems). The health professionals enter the data about the patient’s characteristics and information about their quit attempt using the supplied on-line template, via the Pen CS iSISTAQUIT Topbar app or web-link version or via the Communicare iSISTAQUIT clinical item. Quarterly aggregated data will be created within Microsoft PowerBI for the Pen Cs Topbar App template. Services that do not have access to electronic clinical information systems utilising Pen CS Topbar app or Communicare template will be provided with an alternate method to record the data from the iSISTAQUIT template during the consultation with the patient. The quarterly aggregated data report will then be generated by the health service using R/RStudio.

At the end of the study, qualitative interview data with health practitioners, managers, and champions will be collected and analysed by an external research agency to prevent bias.

#### Evaluation plan

iSISTAQUIT training: Evaluation will be done using the RE-AIM framework, which systematically evaluates the Reach, Effectiveness, Adoption, Implementation and Maintenance of implementation studies. For details see, Table 2.

Descriptive statistics will be used to present numbers, rates, proportions and trends in the data collected through surveys, Likert scales and service level data available through data collection tools described in Table 2. Thematic analysis will be used to analyse qualitative data collected during end of study interviews with practitioners, managers and research facilitators at the services.

Knowledge, attitudes and practices related to SCC: Differences in practitioner online survey responses from pre-training (referent period) to immediate post- and 3 months post-training will be assessed using linear mixed effects regression models, including fixed categorical effects for time, and a random intercept for site to model correlated responses for practitioners from the same service.

Social media campaign: The success of social media campaign will be assessed using surveys, qualitative methods, and social media metrics. More details are available from Table 3.

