#### Sample size

This project will implement the SISTAQUIT intervention in ACCHOs and Mainstream Health Services/sites. Sample size proposed is 10 of each health service or sites (N = 20), however if the demand is higher, we will aim to accommodate more services for the training, up to 30. With 20 sites, assuming an average of 8 HCPs trained per site are assessed for knowledge, attitudes and practices pre and post intervention, the study will have 90% power to detect a small to moderate standardised effect size of 0.2 standard deviations, with a 5% type 1 error rate.

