#### Option 1. Evaluation research package

HCPs will be required to consent to completing the self-paced training modules, the reflective workbook and the pre- and post-training surveys (4 surveys in total). The training surveys will provide evidence on changes in knowledge, attitude and behaviours of the HCPs related to smoking cessation care. HCPs will be entered into a prize draw for completing all surveys and will have an option to claim CPD points.

The full iSISTAQUIT Evaluation-Research package consists, in addition to the training resources (treatment manual, patient flipchart and My Journey (patient) booklet), a) the provision of a carbon monoxide meter and oral nicotine replacement therapy (NRT), and, b) the choice of two medical practice software templates (Pen CS Topbar or Communicare) which aid and support the HCPs to enter the data about the patient’s medical consultation and the characteristics of the women’s quit attempts. The templates will be also utilised to guide the consultation according to the training using the ABCD approach [43]. ABCD approach stands for A—ask/assess; B—brief advice; C—cessation; and D—discuss the psychosocial context of smoking. This approach has been previously used in ICAN QUIT in Pregnancy and the SISTAQUIT RCT project.

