### Outcome measures for iSISTAQUIT

#### Outcomes related to RE-AIM framework

This study will utilise the RE-AIM framework (Reach, Effectiveness, Adoption, Implementation and Maintenance) to plan, evaluate and report the intervention impact of the implementation of iSISTAQUIT (See Table 2). RE-AIM framework was chosen as it is a widely used implementation model that reports comprehensively on the key issues related to implementation studies- beginning with adoption and reach, followed by implementation and efficacy or effectiveness, and finishing with maintenance [46].

**Table 2 pone.0274139.t002:** RE-AIM framework evaluation.

RE-AIM component	Outcomes	Method of assessment (data sources)	Data sources
Reach	1. Service participation rate	• Number of HS participating in Evaluation-Research package / Number of HS approached (CL, RF) • Number of HS participating in Training only package/ number of HS approached (PTA, CCI)	• PenCS Topbar application or web-based version for iSISTAQUIT (ABCD template) or • Communicare iSISTAQUIT Clinical item (ABCD template)
	2. HCP participation rate	Number of HCP registered to do the training/ number of HCPs determined to be eligible to participate by the service (OM, RF)	
	3. Representativeness	Characteristics of HCPs such as age, sex and region of practice compared with national/regional figures available through national databases and peak bodies data (such as the General Practice Workforce providing Primary Care services in Australia)	Australian Government DOH General Practice Workforce providing Primary care services in Australia (https://hwd.health.gov.au/resources/data/gp-primarycare.html)
Effectiveness	1. Barriers and enablers	A 9 item, 5-point Likert scale (strongly disagree to strongly agree) questionnaire based on the Theoretical Domain Framework [49]. (OS)	• Online (through Moodle) pre-, immediate post- training and 3-month surveys
	2. Knowledge attitudes and practices related to SCC	Knowledge, Attitudes and Practices related to SCC measured through online pre-, immediate post- and 3 months post-training surveys. (OS)	• Online (through Moodle) pre-, immediate post- training and 3-month surveys

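### The barriers-and-enablers scale is assigned only descriptive statistics, so its pre-to-post change has no planned interval and no protection against selective drop-out

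*Protocol article*

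**What the plan says.** All references are to the protocol article.

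- **Outcome.** Table 2 (Outcomes related to RE-AIM framework) gives barriers and enablers as the first item under Effectiveness: "A 9 item, 5-point Likert scale (strongly disagree to strongly agree) questionnaire based on the Theoretical Domain Framework". KAP is the second item.
- **Timing.** Both items have the same data source: "Online (through Moodle) pre-, immediate post- training and 3-month surveys".
- **Respondents.** Under Option 1, Evaluation research package, HCPs consent to completing "the pre- and post-training surveys (4 surveys in total"). The data are therefore repeated measures on the same people.
- **Descriptive rule.** The Evaluation plan states: "Descriptive statistics will be used to present numbers, rates, proportions and trends in the data collected through surveys, Likert scales". The sentence goes on to include service-level data from the tools in Table 2.
- **Model.** A separate paragraph in the same section begins: "Knowledge, attitudes and practices related to SCC: Differences in practitioner online survey responses from pre-training (referent period"). It specifies a linear mixed model with time as a categorical fixed effect and "a random intercept for site to model correlated responses for practitioners from the same service". No HCP-level term is mentioned.
- **Power.** The Sample size section refers only to KAP: "With 20 sites, assuming an average of 8 HCPs trained per site are assessed for knowledge, attitudes and practices pre and post intervention", with "90% power to detect a small to moderate standardised effect size of 0.2 standard deviations, with a 5% type 1 error rate".

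**The concern.** Two sibling outcomes come from the same questionnaires, people and time points, yet only one has a model attached by name. The model paragraph carries the name of Table 2's second effectiveness item. The barriers scale is the effectiveness item that Table 2 describes as a Likert scale, and Likert scales are named in the descriptive sentence. No reason is given for treating the two differently.

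The study has one arm, so pre-to-post change is all the evidence of effect this scale can offer. A described trend raises two issues:

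1. If each survey is summarised over whoever answered it, a change in who answers can look like a change in barriers. If less engaged HCPs skip the 3-month survey, the trend improves with no true change. If the better-placed ones skip it, the trend worsens.
2. A described trend comes with no interval, so the reader cannot tell a real shift from noise.

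**Working it through.** **The plan's own figure.** The documents give no figure for this scale. The nearest is the 90% power for KAP with 20 × 8 = 160 HCPs and 0.2 SD. With a paired comparison, two-sided 5% and no clustering of change, power = Φ(0.2 × √160 / √(2(1 − r)) − 1.96), where r is the pre-post correlation.

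- r = 0.5: Φ(2.530 / 1.000 − 1.96) = Φ(0.570) = 72%
- r = 0.7: Φ(2.530 / 0.775 − 1.96) = Φ(1.306) = 90%

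The stated 90% is reached at r of about 0.70. The article does not give r, so the figure can be neither confirmed nor refuted. It was not computed for the barriers scale in any case.

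**Drop-out.** Let p be the proportion answering at 3 months, and let m_R and m_N be the baseline means of later responders and non-responders. Suppose nobody changes.

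- Baseline mean over everyone: p·m_R + (1 − p)·m_N
- 3-month mean over responders: m_R
- Apparent change: m_R − p·m_R − (1 − p)·m_N = (1 − p)(m_R − m_N)

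Neither p nor the gap is in the documents, so both are assumptions:

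| Response at 3 months | Gap 0.2 SD | Gap 0.5 SD |
|---|---|---|
| 80% | 0.20 × 0.2 = 0.04 SD | 0.20 × 0.5 = 0.10 SD |
| 60% | 0.40 × 0.2 = 0.08 SD | 0.40 × 0.5 = 0.20 SD |

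At 80% response, an artefact of 0.20 SD would need a gap of 0.20 / 0.20 = 1.0 SD.

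**Precision.** With complete data, the difference between two wave means equals the mean of the within-person differences. It is the same estimate, with the same sampling variance 2(1 − r)/n in SD² units. Pairing therefore affects the interval attached to the estimate, not the estimate itself. For n = 160, ignoring clustering of change by site:

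- SE that respects pairing, r = 0.5: √(2 × 0.5 / 160) = 0.079 SD, 95% half-width 1.96 × 0.079 = 0.155
- SE that respects pairing, r = 0.7: √(2 × 0.3 / 160) = 0.061 SD, 95% half-width 1.96 × 0.061 = 0.120
- SE that ignores pairing: √(2 / 160) = 0.112 SD, 95% half-width 1.96 × 0.112 = 0.220

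The values of r are assumptions. The last line shows what a reader would get by forming an interval from separate wave summaries. The plan proposes no such calculation.

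**Would the KAP model as written be enough?** No. With a site intercept only, an HCP's three answers are treated as independent given site. The model does not link a non-responder's baseline to the missing 3-month value, so selective drop-out within a site stays in the time effect. The SE also ignores within-person pairing. An HCP-level random effect is needed for both purposes.

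**The case against.** The strongest reply is that the article does not say what the concern needs it to say. The descriptive sentence is an umbrella over all the quantitative sources, including the KAP surveys that are also modelled, so falling under it does not exclude modelling. The model sentence speaks of practitioner online survey responses, and the barriers items come from those surveys. No primary outcome is named and no power is attached to this scale, so description is a legitimate choice. A condensed article may also leave such detail to an unseen analysis plan.

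Much of this stands. A reader might infer that the plan fixes separate, unmatched summaries at each wave. It does not: it promises trends, which could be shown in matched respondents, so the drop-out argument is conditional. Being listed first does not make the scale primary. The consent to complete the surveys, and the prize draw for completing all of them, may hold response up.

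What does not stand is that this is merely an omitted detail. The Evaluation plan does allocate analyses. It names Likert scales under description and heads the model with the name of the other outcome. If the model was meant to cover both, its label is wrong, and the missing HCP term would still have to be added.

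**Conclusion.** The point holds as a modest improvement. On the natural reading, the barriers scale receives descriptive statistics only, so no interval for its change is planned and nothing guards against selective drop-out. If wave summaries use all available respondents, the artefact runs from 0.04 SD (80% response, 0.2 SD gap) to 0.20 SD (60%, 0.5 SD). Those inputs are illustrative and not drawn from the documents.

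Three stronger readings are not supported:

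- **Precision is thrown away.** With complete data the point estimate is the same either way; what is missing is a valid interval.
- **Drop-out could mimic the effect the study is powered for.** The 0.2 SD in the Sample size section belongs to KAP, and the 0.20 SD result depends on the assumptions chosen.
- **Heavy drop-out is already visible.** The 42 of 92 HCPs under Status and timeline had completed training while recruitment continued. That is not survey non-response.

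**What to change.** State in the Evaluation plan that the 9-item score will be analysed with a linear mixed model using the KAP contrasts: pre to immediate post, and pre to 3 months. Include random intercepts for both site and HCP; copying the KAP model with its site intercept alone would not be enough. Report each change with a 95% CI beside the descriptive tables, and label the analysis supportive, since no power or primary status attaches to this scale.

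This uses HCPs with partial responses and limits drop-out bias if missingness depends on observed answers (missing at random). It does not remove bias from drop-out that depends on unobserved 3-month answers.

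The cost is one additional model with one more random effect than the KAP model now has. No new data are needed.

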### Training delivery

Both training packages with the associated options will be available through the Moodle platform provided by the Hunter Postgraduate Medical Institute (HPMI). Moodle is a robust, secure, and integrated system learning platform for educators, administrators and learners. Moodle will be used for the associated training surveys (see https://moodle.com/security-privacy/) and participants will need to make an account to log into the HPMI website to access the online training and the surveys.

iSISTAQUIT training for both packages will have 14 e-Learning modules, taking approximately four hours to complete. The training will be internet-enabled and self-paced and includes videos, text, and interactive elements, supported by hardcopy resources i.e., the treatment manual and patient flipchart for HCPs and the My Journey (patient booklet), which includes augmented reality videos to aid smoking cessation care. The iSISTAQUIT e-Learning is designed to use the Eight Aboriginal Ways of Learning, is self-paced and accredited for professional development or CPD points with several professional colleges [44]. The Eight Aboriginal Ways of Learning involves using an Aboriginal pedagogy (such as story sharing, community links and symbols and images) and is congruent with the Australian Health Practitioner Regulation Agency (AHPRA) framework for cultural safe practice by HCP’s [44, 45].

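### The pre/post survey model has a random intercept for site but none for practitioner, so the standard errors of its time contrasts are wrong

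*Protocol article*

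**What the plan says.** The Evaluation plan section of the protocol article analyses knowledge, attitudes and practices with a linear mixed effects regression. It compares survey responses "from pre-training (referent period) to immediate post- and 3 months post-training". The model is described as "including fixed categorical effects for time, and a random intercept for site to model correlated responses for practitioners from the same service". No practitioner effect, within-person covariance or robust variance is mentioned.

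The surveys are repeated on the same people. Under Option 1 (Evaluation research package) each practitioner consents to four surveys in all. Under Training delivery, "participants will need to make an account to log into the HPMI website to access the online training and the surveys", so the waves can be linked within person.

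The Sample size section counts practitioners in pairs of assessments: "With 20 sites, assuming an average of 8 HCPs trained per site are assessed for knowledge, attitudes and practices pre and post intervention". Taking the type 1 error as 5%, it then says that "the study will have 90% power to detect a small to moderate standardised effect size of 0.2 standard deviations". It gives no within-practitioner correlation and no site ICC, and does not say whether the SD is that of the score or of the change.

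**The concern.** A change from before to after training is a within-person contrast. Stable differences between practitioners cancel from it when each person serves as their own control. With site as the only random effect, those differences stay in the residual and are charged to the standard error of the contrast. The stated purpose of the site intercept, correlation between colleagues, is a different source of correlation and does not cover this one.

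Two further consequences follow.

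- If some practitioners skip the 3-month survey, the model in effect compares all baseline respondents with a selected group at 3 months, because nothing ties a person's later answer to their earlier one.
- A site intercept does not allow sites to differ in how much they change. That omission makes the standard error too small, which works against the first error.

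This is the only inferential analysis the article specifies for the Effectiveness outcomes, and the Conclusion says the results will inform a scale-up project. Real change could be missed, or selective 3-month response could look like a training effect.

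**Working it through.** **Inputs from the protocol.** 20 sites x 8 practitioners = 160; three waves; effect 0.2 SD; 5% type 1 error (taken as two-sided); stated power 90%.

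**Assumed, because not stated.** Total SD 1; site ICC 0.05 (0 to 0.20 also tried); within-practitioner correlation r of 0.4 to 0.8; normal approximation.

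**Step 1: the protocol's 90%.**

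- Two waves treated as independent: SE = sqrt(2/160) = 0.112, power 43%.
- 0.2 read as SDs of the change: SE = 1/sqrt(160) = 0.079, power 72%.
- Paired, 0.2 SD of the score: SE = sqrt(2(1 - r)/160). For 90% power the SE must be 0.2/(1.960 + 1.282) = 0.0617, so 1 - r = 0.0617² x 160/2 = 0.305 and r is about 0.70.

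The stated inputs alone do not give 90%. Pairing with r near 0.70 does. The figure is therefore neither confirmed nor shown wrong.

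**Step 2: standard error reported by the site-only model, equal change across sites.** Let the practitioner variance be vp = r - ICC and the residual variance ve = 1 - r. The within-site degrees of freedom are 480 - 20 - 2 = 458, of which 20 x 7 = 140 lie between practitioners and 318 do not. The expected residual mean square is

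MS = [140(3vp + ve) + 318ve]/458.

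The reported SE is sqrt(2MS/160) and the true SE is sqrt(2ve/160).

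For r = 0.5: MS = [140(1.35 + 0.50) + 318 x 0.50]/458 = 418/458 = 0.913. The reported SE is 0.107, the true SE 0.079, the ratio 1.35.

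Actual power is Phi((0.2 - 1.96 x reported SE)/true SE). With a practitioner intercept it is Phi(0.2/true SE - 1.96).

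| r | Reported SE | True SE | Ratio | Power, site only | Power, practitioner intercept |
|---|---|---|---|---|---|
| 0.4 | 0.107 | 0.087 | 1.24 | 45% | 64% |
| 0.5 | 0.107 | 0.079 | 1.35 | 45% | 72% |
| 0.7 | 0.106 | 0.061 | 1.73 | 45% | 90% |

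The relative loss of power is 29%, 37% and 50%. For ICC 0 to 0.10 and r from 0.4 to 0.8, site-only power stays below 50%; at ICC 0.20 it is 53% to 58%. At r = 0.7 the actual type I error is 2(1 - Phi(1.96 x 1.73)), about 0.07% instead of 5%.

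**Step 3: sites that differ in change.** Let t be the between-site SD of change. The true SE becomes sqrt(2(1 - r)/160 + t²/20), with the reported SE held at its Step 2 value (an approximation).

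| t | True SE, r = 0.5 | Ratio | True SE, r = 0.7 | Ratio |
|---|---|---|---|---|
| 0.3 | 0.104 | 1.03 | 0.091 | 1.17 |
| 0.4 | 0.119 | 0.89 | 0.108 | 0.98 |

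**Step 4: 3-month non-response.** The document gives no response rate, so this is illustration only. Assume no true change, about 60% response at 3 months, and log-odds of response rising by 0.7 per SD of baseline score. In simulation the site-only model then gives a 3-month change of about +0.10 to +0.15 SD for r = 0.5 to 0.7, while a practitioner intercept gives about zero. The second result holds because missingness was made to depend only on an observed score.

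**The case against.** **The article is condensed.** The model takes one sentence, its list of terms may not be exhaustive, and a fuller plan could add a practitioner effect. That is possible. But the sentence names the random effect and the correlation it is meant to handle, which is between colleagues. Followed as written, it does not fit repeated surveys of one person.

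**The error is conservative.** With complete data and equal change across sites, the estimates are unbiased and false positives fall. This stands. A reader might infer that the model inflates false positives in general; the check does not support that. It can do so only through selective 3-month response or through site differences in change.

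**The size is uncertain.** This also stands. A reader might infer that half the power is lost. That holds only near r = 0.7, and linking that value to the protocol's 90% is an inference that requires 0.2 SD to refer to the score. A reader might also infer that intervals are bound to be far too wide. Step 3 shows that moderate site differences in change remove most or all of the excess.

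**Non-response may be slight.** Option 1 practitioners consent to all surveys and enter a prize draw for completing them. This could keep response high; the document does not say what response is expected.

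**Little hangs on the p-value.** The study is single-arm, the RE-AIM evaluation is largely descriptive, and no decision rule is tied to this test. That lowers the severity but does not make the model right.

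**Conclusion.** The model as written omits the practitioner level of a repeated-survey design, and the standard errors of its time contrasts are wrong. If sites change equally and the ICC is 0.05, they are too large by a factor of 1.24 to 1.73 for r between 0.4 and 0.7, and power for 0.2 SD is about 45% where a practitioner intercept would give 64% to 90%. Both r and the ICC are assumptions. The net direction is not certain, because a between-site SD of change of about 0.3 to 0.4 shrinks or reverses the excess. The 3-month contrast is open to bias when response depends on earlier scores, by an amount the document does not allow anyone to fix. The check does not show the 90% power statement to be wrong; it shows only that, if 0.2 SD refers to the score, the figure needs a pairing that the stated model discards. Severity: should fix.

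**What to change.** Replace the model sentence in the Evaluation plan with a linear mixed model that has:

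- categorical time as the fixed effect;
- a random intercept for site;
- a random intercept for practitioner nested in site, with waves linked by Moodle account and every practitioner with at least one survey included;
- a site-by-time random effect, or site-clustered standard errors with a small-sample correction.

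State that the 3-month estimate relies on missing at random given the observed surveys. A practitioner intercept does not remove bias if response depends on unobserved 3-month scores. In the Sample size section, state the within-practitioner correlation and site ICC behind the 90%, and whether 0.2 SD refers to the score or the change.

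The cost is a few sentences. No new data are needed, since the surveys already sit behind individual accounts.
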